### Sample size calculations

The sample size calculations are based on the expected difference in self-reported point prevalence abstinence (PPA) six months after the targeted quit between the intervention and control groups. Based on data from STOPbasen and international literature [14,19], the abstinence rate under the intention-to-treat analysis (ITT) approach is estimated to be 23% in the control municipalities and 34% in the intervention municipalities. The power calculations incorporate an intraclass correlation coefficient (ICC) of 0.05 to account for expected similarities among participants within clusters. This adjustment reflects the likelihood that young people within the same municipality receive support from the same youth coach/cessation counselor and are exposed to the same contextual environment (e.g., schools or other youth arenas). Despite extensive follow-up procedures, a 20% loss to follow-up is expected and is included in the sample size estimation [20]. Based on these assumptions, each municipality must include at least 27.8 youth participants in cessation activities during the entire intervention year, a total of 1,526 youth participants.

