#### C. Cessation.

The cessation course consists of seven meetings planned over eight weeks. The sessions last between 1.5 hours and 45 minutes. It is advised that approximately twelve young people are recruited for each course established. Participating municipalities can recruit and create as many courses as they wish during the intervention year.

The course is anchored around key constructs from social cognitive theory and posits that learning occurs in a social context with a dynamic and reciprocal interaction of the person, environment, and behavior [21]. Peer elements are used both in recruitment and in group counseling. The approach to young people stems from theories of cognitive behavioral therapy [22], as well as narrative engagement theory [23]. Furthermore, the course is based on the International Child Development Programme (ICDP) and its eight interaction themes as a tool for relationship- and resource-oriented practices [24]. The exercises stem from mindfulness-based cognitive therapy [25] and mindfulness-based stress reduction [26].

As part of the cessation course, a newly developed score (The U-Niko score, validated by 25 young people, S3) is used to measure physical nicotine dependence. The score has been developed because the nationally used Fagerström score is not suitable for youth, since many young people use more than one tobacco and nicotine product, the consumption of e-cigarettes is difficult to measure, and the nicotine content in e-cigarettes and nicotine pouches can vary significantly. The U-Niko score consists of five short questions ranging from to 0–9, with 9 being the highest. A score of ≥ 6 indicates high physical nicotine dependence, suggesting that nicotine patches may be beneficial as a part of the cessation process. For individuals aged 18 + years with a nicotine patch allergy, cytisine is recommended for those with a score of ≥6.

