#### C. Cessation.

At the first cessation session, all participants in both the intervention and control municipalities will complete a baseline questionnaire on contact information, personal characteristics, information on tobacco and/or nicotine use, and the U-Niko score. The baseline questionnaire also contains a consent form for participation in the study. The baseline questionnaire will be registered in STOPbasen.

Further, the young participants in the intervention group will be invited to answer a short online survey on their experiences with the intervention after the course has ended (4 weeks post-target quit date), regardless of their tobacco and nicotine status.

Six months after the targeted quit date, all participants (in both the intervention and control groups) will be contacted by phone to examine the long-term effects of the cessation offer. A research assistant will contact the participants multiple times by phone and send text messages to decrease the number of missing values at follow-up.

All participants will be informed that each completed questionnaire (baseline survey, post-intervention survey (only intervention group), and six-month follow-up survey) will be entered into a raffle with the chance to win a gift certificate worth 1000 DKK (~134 euros/139 USD). In total, six participants from the intervention municipalities and four from the control municipalities will be drawn to win.

Participants who report being tobacco- and nicotine-free at the six-month follow-up will be invited to undergo a saliva cotinine test to validate their abstinence. The saliva test will be mailed to each participant who has agreed to participate and will be conducted via an online interview using Teams. The participant will take the test and show the answer to the research staff during the online meeting, discard the test, and receive a gift certificate for 300 DKK (~40 euros/42 USD), regardless of the outcome of the validation test.

The primary outcome is *the effect of the cessation course,* which will be measured using *long-term self-reported PPA* (not using any tobacco or nicotine product in the last 14 days) six months after the targeted quit date in the intervention municipalities compared with the control municipalities. To assess this, participants will be asked, “Have you used any tobacco or nicotine products in the last 14 days?” (Yes/No).

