The secondary outcomes are *short-term self-reported abstinence* (i.e., at the end of the cessation course/counseling), *continuous self-reported abstinence* (from targeted quit date to six-month follow-up), and v*alidated PPA,* which will be assessed in all participants who report being tobacco and nicotine abstinent at the six-month follow-up and agree to participate in the cotinine validation process.

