#### C. Cessation.

The analyses of the primary outcome on self-reported 14-days PPA at six months follow-up will follow the intention-to-treat (ITT) principle, assuming that all non-respondents are currently smoking or using nicotine. Data will be analyzed using a generalized linear mixed model (GLMM) to account for clustering, recognizing that youth participants within the same municipality may be more similar to each other than to participants from other municipalities. Results will be presented in a table as odds ratios (ORs) for 14-day PPA at six months after the targeted quit date, with corresponding 95% CIs. A p-value < 0.05 will be considered statistically significant.

Secondary outcomes, including short-term self-reported abstinence, continuous self-reported abstinence, and validated 14-days PPA at six months follow-up, will be analyzed using the same GLMM approach as for the primary outcome and presented in tables as ORs with corresponding 95% CIs. In addition, a table will present and compare the baseline characteristics of all youth participants between the intervention and control groups, including age, educational level, type of nicotine product used, and follow-up participation rates.

Given the high degree of data completeness in STOPbasenwe intend to employ a complete case analysis, excluding patients with any missing values in the included variables from the analysis (listwise deletion). Consequently, a sensitivity analysis using an as-observed approach will be conducted, including only participants with a valid follow-up. Sensitivity analyses will be performed using the final adjusted model from the main analyses. This approach builds on the assumption that data is Missing Completely At Random (MCAR). However, when it comes to smoking status, data are more likely to be Missing Not At Random (MNAR). Therefore, if necessary, considering the number of missing values and loss to follow-up, a sensitivity analysis using a chained multiple imputation model will be conducted based on the final adjusted model in the main analyses.

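### The denominator of validated abstinence is not secured: read literally, the arms are compared among tested abstainers only, and on the alternative reading those who decline the test have no code

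*Protocol article*

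**What the plan says.** Under Measures and data assessment, C. Cessation, the protocol article sets out the procedure: "Participants who report being tobacco- and nicotine-free at the six-month follow-up will be invited to undergo a saliva cotinine test to validate their abstinence". Those who report use are not invited. The same section then lists validated PPA among the secondary outcomes, as one "which will be assessed in all participants who report being tobacco and nicotine abstinent at the six-month follow-up and agree to participate" in the validation process.

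The Data analysis plan, C. Cessation, makes three statements that bear on this outcome:

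- The analyses of the primary outcome, self-reported 14-day PPA, "will follow the intention-to-treat (ITT) principle, assuming that all non-respondents are currently smoking or using nicotine".
- The secondary outcomes, validated PPA among them, "will be analyzed using the same GLMM approach as for the primary outcome", with ORs and 95% confidence intervals.
- A complete-case analysis is intended, "excluding patients with any missing values in the included variables".

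No sentence gives the denominator for validated PPA. None says how to code a participant who reports use, or one who reports abstinence and declines the test.

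**The concern.** Two quantities could carry the name validated PPA. One is the share of all enrolled youth who report abstinence and have it confirmed, which measures cessation. The other is the share of tested abstainers whose test is negative, which measures how far self-report can be trusted. The second is conditional on the outcome itself and on willingness to be tested, both determined after randomisation, so its arm comparison does not estimate the effect of the course on abstinence.

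The wording permits the second quantity and, taken at face value, leads to it. Assessment is confined to consenting abstainers, everyone else lacks a cotinine result, and missing values lead to deletion. The saliva test is the only biochemical check that the article describes on the self-reported primary cessation outcome. An OR near 1 from a tester-only model could be read as contradicting a true primary result.

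**Working it through.** **Inputs from the article.** Self-reported abstinence under ITT is "estimated to be 23% in the control municipalities and 34% in the intervention municipalities". There are 1,526 youth in 55 municipalities (27 intervention, 28 control), an "intraclass correlation coefficient (ICC) of 0.05" and 20% loss to follow-up.

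**Assumed, not in the article.** Test uptake *u* among self-reported abstainers (40–80%) and confirmation *c*, the share of tests that are negative (70–90%).

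**Step 1: the article's own figure.** It gives none for validated PPA. Its total for the primary outcome is reproduced closely if 80% power and a two-sided 5% test are assumed:

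- Per arm, without clustering: n = (1.960 + 0.842)² × (0.34×0.66 + 0.23×0.77) / 0.11² = 260.4.
- With *m* enrolled per municipality: 0.8 × 55 × m = 2 × 260.4 × [1 + 0.05(m − 1)], so m ≈ 27.6 and the total is about 1,516, against the stated 27.8 and 1,526.

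The planned rates and N are therefore a sound basis for what follows.

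**Step 2: who would be tested.**

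- Enrolled: 1,526 × 28/55 = 777 control; 1,526 × 27/55 = 749 intervention.
- Self-reported abstainers: 777 × 0.23 ≈ 179; 749 × 0.34 ≈ 255.
- Tested at u = 60%: about 107 control and 153 intervention.

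**Step 3: testers only.** The outcome proportion is *c* in each arm, so OR = [c_I/(1 − c_I)] / [c_C/(1 − c_C)]. Self-reported abstinence does not enter the formula.

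- c equal in both arms: OR = 1.00 at any uptake and for any difference in abstinence.
- c = 80% intervention, 85% control: OR = (0.80/0.20)/(0.85/0.15) = 0.71. The all-enrolled OR at 60% uptake, with proportions 0.34×0.6×0.80 = 16.3% and 0.23×0.6×0.85 = 11.7%, is 1.47.

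**Step 4: all enrolled, untested counted as not validated.** The proportion is s × u × c, where *s* is self-reported abstinence.

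| u | c | Control | Intervention | OR |
|---|---|---|---|---|
| 40% | 70% | 6.4% | 9.5% | 1.53 |
| 60% | 80% | 11.0% | 16.3% | 1.57 |
| 60% | 85% | 11.7% | 17.3% | 1.58 |
| 80% | 90% | 16.6% | 24.5% | 1.63 |

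For comparison, the self-reported OR is (0.34/0.66)/(0.23/0.77) = 1.72.

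**Step 5: the coding of decliners matters.** Keep the all-enrolled denominator, count decliners as failures, hold c = 85% and let uptake differ by arm:

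- 60% control, 41% intervention: 11.7% versus 11.8%, OR 1.01.
- 50% control, 60% intervention: 9.8% versus 17.3%, OR 1.94.

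If each arm's confirmation rate is instead applied to its untested abstainers, the proportions are 0.23×0.85 = 19.6% and 0.34×0.85 = 28.9%. The OR is then 1.67 whatever the uptake.

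**The case against.** The strongest reply is that the article never sets a tester-only denominator. The outcome definition may say only who receives the test, repeating the procedure. A participant who reports use needs no test to be classed as non-abstinent, and a prevalence of abstinence among people already selected as abstinent would hardly be a prevalence. Using the same modelling approach as the primary outcome may bring its ITT rule with it. The listwise-deletion sentence is justified by completeness of the national database, and nothing says that cotinine results are held there. Nor can that sentence apply literally to outcomes, since it would remove the very non-respondents whom the primary analysis counts as using.

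Much of this stands. The all-enrolled reading is available, so a reader who infers that the plan definitely measures truthfulness among testers goes further than the text. But that reading is not secured either. ITT is attached by name to the primary outcome only, and its failure rule covers non-respondents. Someone who answers the six-month call, reports abstinence and declines the test has responded, so the rule does not reach that person.

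Two further replies:

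- Coding a secondary endpoint is often left to the analysis plan. Here, though, the article itself states the assessed group, the model and the missing-data rule, and it is their combination that misleads.
- The tester-only OR of 1.00 follows from assuming equal confirmation. That is correct, but under unequal confirmation the OR reflects only the difference in confirmation (Step 3).

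A reader might also infer that nicotine patches, described as "suggesting that nicotine patches may be beneficial as a part of the cessation process", would make the test uninterpretable. The documents do not support that. The course is planned over eight weeks, the test follows the six-month contact, and nothing indicates that patches are still in use then.

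**Conclusion.** The point holds as an insecure definition that admits two materially different analyses. Read literally, the arms are compared among tested abstainers, with OR 1.00 under equal confirmation at the planned 34% versus 23%. If ITT carries over and untested abstainers count as failures, the OR is about 1.5 to 1.6 across the assumed equal uptake of 40–80% and confirmation of 70–90%. Even then the treatment of decliners is unstated, and with unequal uptake the OR can run from about 1.0 to 1.9.

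Uptake and confirmation are assumptions throughout, and the article gives neither. That a tester-only OR carries no information on how many youth quit does not depend on them.

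Testing only those who claim abstinence is not an error, and a reader should not infer one. The fault lies in the denominator and the coding. The outcome is secondary, and the primary analysis and the sample size are unaffected. The change should be made before the data are analysed.

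**What to change.** - Define validated 14-day PPA over all enrolled participants, with success meaning self-reported abstinent and cotinine-negative.
- Count self-reported users, non-respondents and untested abstainers as not validated. Abstainers with a positive test are failures by the same definition.
- State that listwise deletion does not apply to this outcome.
- Report test uptake among self-reported abstainers, and confirmation among those tested, separately by arm. The confirmation rate remains useful as a description of self-report quality.
- Add a sensitivity analysis that applies each arm's confirmation rate to its untested abstainers.

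The cost is a few sentences and one extra analysis, with no additional data collection. There are two downsides. Validated rates will look lower because decliners count as failures, and the main OR becomes sensitive to differential uptake, as Step 5 shows. The uptake report makes the second visible. The sensitivity analysis addresses it, on the assumption that untested abstainers would be confirmed as often as tested ones.

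The comparison should also be presented as supportive. At 60% uptake and 85% confirmation, with the planned ICC and all 1,526 enrolled (design effect 1 + 26.745 × 0.05 = 2.34, so about 326 effective participants per arm), power to detect 11.7% versus 17.3% is about 53%.

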### Additional measures

Additional measures of the participants will be assessed in the baseline survey, including demographic information such as age, sex, gender, socioeconomic status, U-Niko dependence score, and product use (type, frequency, and duration). Furthermore, data on the employment of youth participants at baseline will be obtained from the Danish Education Register.

Additional measures for youth cessation counselors will be assessed during the post-intervention municipal follow-up survey. These measures include education and previous experience with tobacco and nicotine cessation activities.

### Data analysis plan

#### A. Training.

A table will present the characteristics of the counselors separately for the intervention and control municipalities, including gender, age, education, years of experience with youth, and experience with tobacco and/or nicotine cessation. The effect of training new youth counselors will be assessed by comparing their self-efficacy scores in the intervention and control municipalities after the intervention year. Because counselors are nested within municipalities, and municipalities are the unit of randomization, a linear mixed-effects model (LMM) with a random intercept for municipalities will be used to account for clustering. The model will be adjusted for counselor characteristics, such as counselor education, years of experience working with youth, and years of experience in tobacco and/or nicotine cessation.

Results from the LMM will be reported as estimated mean differences with 95% confidence intervals (CIs), and a p-value < 0.05 will be considered statistically significant.

#### B. Recruitment.

A table will present and compare relevant covariates between the intervention and control municipalities, including municipality size, socioeconomic indicators, funding received from the Danish Health Authority, previous experience with youth cessation counseling, and youth population. The effect of the recruitment strategy will be assessed by comparing the number of youths recruited for cessation activities in the intervention and control municipalities using an LMM. The model will be adjusted for relevant covariates, including the number of youths recruited in each municipality in the previous year (2024), municipality size, and whether the municipality received funding from the Danish Health Authority for youth-related cessation activities.

Results from the LMM will be reported as estimated mean differences with 95% CIs, and a p-value < 0.05 will be considered statistically significant.

Secondary results describing the absolute change in the number of youths recruited for cessation activities between 2024 and 2025 in intervention municipalities will be presented using descriptive statistics in a table, with the results shown separately for each municipality.

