## Methods

### Study design

This study is a cluster randomized controlled trial (RCT) including 55 Danish municipalities and aimed at youth aged 16–25. The intervention period will run from January 1, 2025, to December 31, 2025. The municipalities were randomly allocated to either the U-Niko intervention group or the control group in the spring of 2024. The youth participants will receive either the U-Niko intervention or a control condition (municipal cessation activities as usual, described under the section *Intervention*) based on the municipality in which they live, go to school, work, or, in some other way, have their daily activities. “Cessation activities” are defined as counselling processes over several sessions, not brief advice.

The study is a field trial in which all intervention activities are performed by municipalities, not researchers. The intervention municipalities will not receive any economic or manpower support from the research group.

Recruitment and cessation counseling will be conducted via the municipalities and will occur during the entire intervention year from January 1, 2025, to December 31, 2025. Enrollment and follow-up assessments will be conducted via the municipalities in cooperation with the national database on tobacco and nicotine cessation (STOPbasen) and the research group. STOPbasen is a Danish database where most cessation activities in Denmark are routinely registered and have high validity. Data collection is estimated to be complete in June 2026, with results expected to be ready to publish approximately 6–12 months later (Fig 1).

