#### B. Recruitment.

Data on the number of recruited youths will be registered in STOPbasen. The primary outcome is t*he effect of the recruitment strategy,* which will be assessed by comparing the number of recruited youth participants in the intervention municipalities with the control municipalities.

The secondary outcome is the *change in the number of youth recruited* for cessation activities in the intervention group between the intervention year 2025 and the previous year 2024

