Because the study is a field trial and the intervention occurs in a real-life setting, there are also some uncertainties regarding the comparison groups, data registration, and follow-up [29]. The youth-oriented cessation activities in the municipalities have been very sparse in the last few years, and there is a risk that only a few young persons will be included in 2025, resulting in too low a power to detect significant differences between the intervention and control municipalities. However, in early 2024, the Danish Health Authorities launched a call in which municipalities interested in improving their work with youth tobacco and nicotine cessation activities could apply for funding. In total, 58 million DKK (~7,7 million euros) were allocated to this work and funding must be used between fall 2024 and 2027. This may have a negative impact on the study, as some municipalities will have a much higher activity level than anticipated. Nonetheless, both the intervention (~44%, n = 12/27) and control municipalities (~54%, n = 15/28) received funding, and therefore, the hopefully positive effect of the increased resources will be present in both the intervention and control groups. Therefore, it should be feasible that the calculated sample size requirements on 27.8 participants during the whole intervention year in each municipality can be accommodated. The analysis of the effectiveness of the U-Niko intervention (recruitment and cessation) will consider that some of the municipalities (more control municipalities) have received extra funding and, therefore, have more resources.

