Furthermore, the comparison between municipalities that agreed to participate and those that did not highlights important contextual factors that should be kept in mind when interpreting study findings and considering the external validity of the trial. While both participating and non-participating municipalities had on average the same proportion of youths in the target population, indicating a similar level of need, the municipalities that chose to participate were generally larger, and reported more prior experience with cessation activities. Furthermore, municipalities that participated in the study received higher funding from the Danish Health Authority for youth tobacco and nicotine prevention. However, this funding was announced only after the municipalities had enrolled in the study, and they were informed of their funding status only after randomization had been completed. Nonetheless, these differences suggest that participating municipalities may have had greater capacity to implement and deliver cessation interventions. This raises a concern regarding scalability. Although non-participating municipalities have a comparable youth population and thus similar needs, their more limited resources and experience may pose challenges for implementing the intervention in these settings. This should be considered when interpreting the trial’s potential for broader application.

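### The primary recruitment model adjusts for a 2024 count that mostly accrues after the spring-2024 allocation, and the secondary change from 2024 is reported for one arm only

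*Protocol article*

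**What the plan says.** On timing, the Study design section states: "The municipalities were randomly allocated to either the U-Niko intervention group or the control group in the spring of 2024". Invitations went out in March 2024 (Randomization). The same Study design section adds: "The intervention period will run from January 1, 2025, to December 31, 2025".

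The Data analysis plan, B. Recruitment, compares 2025 recruitment between arms with a linear mixed model adjusted for covariates, "including the number of youths recruited in each municipality in the previous year (2024), municipality size, and whether the municipality received funding". It calls for an estimated mean difference, a 95% confidence interval and a 5% significance threshold.

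Under Measures and data assessment, B. Recruitment, the secondary outcome is the change in numbers recruited "in the intervention group between the intervention year 2025 and the previous year 2024". The analysis plan tabulates it descriptively by municipality, again for the intervention arm only. The Abstract names the same outcome without restricting it to one arm.

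On funding, the Discussion says of the grants that "funding must be used between fall 2024 and 2027", that "both the intervention (~44%, n = 12/27) and control municipalities (~54%, n = 15/28) received funding", and of the municipalities that "they were informed of their funding status only after randomization had been completed".

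**The concern.** A covariate in the primary analysis of a randomised comparison should be one that allocation cannot have changed. The 2024 count does not meet that test in full, because it closes on 31 December 2024, months after allocation. The municipalities run all activities themselves, and the caption of Fig 2 lists a preparation stage before the trial activities. An intervention municipality could therefore hold youth courses back until the new programme is available, or begin recruiting early.

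If either happened, the model would compare municipalities at equal 2024 counts when those counts no longer mean the same in the two arms. The distortion would fall on one of the trial's three primary outcomes.

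The secondary outcome has a separate weakness. A rise from 2024 to 2025 in the intervention arm alone cannot be told apart from a general rise. The Discussion itself hopes for a positive effect of the new money in both arms.

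**Working it through.** **1. How much of the covariate follows allocation.** Take spring as March to May. Allocation at the end of March leaves 9 of 12 months after it (75%); at the end of May, 7 of 12 (58%). The remaining 3 to 5 months are a true pre-randomisation baseline.

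**2. How easily the count can move.** The article advises about twelve young people per course (Intervention, C. Cessation), and the sample size section requires 27.8 per municipality per year. One course moved across New Year shifts the 2024 count by about 12, and 12 / 27.8 = 43% of that target. This shows that a shift is possible, not that one occurred.

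**3. Size of the bias if allocation shifts the 2024 count.** Let d be the shift in the intervention arm's mean 2024 count and b the within-arm regression slope of the 2025 count on the 2024 count. Then

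adjusted estimate = true effect − b × d.

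The article gives no counts, so the following are assumptions: underlying municipal recruitment with mean 20 and SD 8; 2025 depends on it with slope 0.8; the 2024 count measures it with noise SD 3; true effect +5 youths per municipality. Then b = 0.8 × 64 / (64 + 9) = 0.70. A simulation of 4,000 trials with 27 versus 28 municipalities agrees:

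| Shift d in 2024 | Formula 5 − 0.70d | Simulated, adjusted | Simulated, unadjusted |
|---|---|---|---|
| −5 | 8.5 | 8.5 | 5.0 |
| −2 | 6.4 | 6.4 | 5.0 |
| 0 | 5.0 | 5.0 | 5.0 |
| +2 | 3.6 | 3.6 | 5.0 |
| +5 | 1.5 | 1.5 | 5.1 |

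**4. A second set of assumptions.** This case has no true effect, control mean 20, and least squares on arm, 2024 count and population, with 500 trials per scenario.

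| 2024 count in intervention arm | d | Mean adjusted difference | Bias per youth shifted |
|---|---|---|---|
| 30% lower | −6 | +5.82 | 0.97 |
| 20% lower | −4 | +3.52 | 0.88 |
| unchanged | 0 | −0.14 | none |
| 20% higher | +4 | −2.97 | 0.74 |
| 30% higher | +6 | −4.21 | 0.70 |

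In the two deferral scenarios, false positives were 12% to 28% against a nominal 5%. The shifts are demanding. With even recruitment and allocation at the end of April, a 30% annual fall needs a fall of 0.30 × 12 / 8 = 45% in the remaining eight months.

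**5. The change from 2024.** A simple change score uses the 2024 count with slope 1, so a between-arm difference in change would carry the full shift, −d. A pre-allocation base would not.

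**6. Funding.** The stated percentages reproduce: 12/27 = 44.4% and 15/28 = 53.6%, a difference of 9.1 points. Fisher's exact test gives a two-sided p of 0.59.

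**The case against.** The strongest reply is that nothing in the article shows that allocation altered 2024 recruitment. All of 2024 precedes the formal intervention period. The months before allocation are a genuine baseline, and control municipalities receive no information about the intervention and carry on as usual. With no shift, both simulations give a bias of about zero. The size of any bias also rests on an assumed mean, assumed shifts and an assumed year-to-year correlation; the Discussion describes youth activity as very sparse, and the new funding could weaken that correlation. All of this stands. A reader might infer that the planned estimate is biased, or that 2024 has no value as a baseline; the article supports neither.

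On funding, a reader might infer from 12/27 against 15/28 that allocation influenced the awards. It does not follow. The money comes from an outside authority under a call launched in early 2024, the imbalance is compatible with chance, and the Discussion says only that municipalities learned their status after randomisation. When a status became known does not show what determined it, and adjusting for a plausible predictor of resources is defensible.

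On the secondary outcome, the table is descriptive, has no test, and the analysis plan does not attribute the change to the intervention. The between-arm question is left to the primary model. That lowers the stakes, but the change remains a named secondary outcome with nothing to set it against.

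**Conclusion.** The point holds as an avoidable risk. The primary recruitment model conditions on a covariate of which roughly 58% to 75% of the months fall after allocation. Any shift that allocation caused in it would bias the effect in the opposite direction, by about 0.7 to 1.0 youths per youth shifted under the assumptions shown. Neither the existence, the direction nor the size of such a shift can be established from the article.

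The one-arm change from 2024 cannot be interpreted as an effect of the recruitment strategy while new funding is available to municipalities in both arms. The funding covariate is a minor matter and not a fault in the primary model. The changes are worth making because they are cheap and remove the question before the results are seen.

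**What to change.** In the primary recruitment model, replace the full-year 2024 count with a pre-allocation count from STOPbasen: 2023 if it is available per municipality, otherwise January 2024 to the allocation date. Keep the 2024-adjusted model as a sensitivity analysis. The Randomization section refers to cessation activity and experience with youths in 2023, but does not confirm that a 2023 count of recruited youths exists for each municipality, so this must be checked first.

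Tabulate the 2024-to-2025 change for both arms with the between-arm difference. The primary model as planned already needs the 2024 and 2025 counts for both arms. Because any shift in 2024 enters that difference in full, show the change from the pre-allocation base beside it where the data allow.

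Funding may stay in the primary model. At most, add a sensitivity model without it.

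The cost is analysis-plan wording and possibly one further data extract. The downside is that an earlier or shorter baseline may correlate less with 2025, with some loss of precision.
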